**Discussion:**

This study will demonstrate if the use of aPRP could reduce the risk of bleeding after aortic surgery compared with ANH. The results are expected to have practical clinical applications in terms of more effective blood protection and shorter hospital stay.

**Trial registration:**

This study was registered with the Chinese Clinical Trial Registry (http://www.chictr.org.cn/) with the ID ChiCTR 1900023351.Registered on May 23, 2019.

**Trial status:**

Recruiting start date: July 1, 2019; expected recruiting end date: July 1, 2024

Version number and date: Version 2 of 05-04-2019

**Supplementary Information:**

The online version contains supplementary material available at 10.1186/s13063-023-07800-4.

## Background

Both acute normovolumic hemodilution (ANH) and autologous platelet-rich plasma (aPRP) have been demonstrated blood-protective effects in cardiac aortic surgery [1, 2]. Platelet-rich plasma (PRP) is a plasma product with a high concentration of platelets that is made by separating fresh whole blood from the patient’s body. Platelets are typically 3–5 times more concentrated in PRP than in normal whole blood, and the key components include platelets, plasma, fibrinogen, leukocytes, and other blood components. Because it is derived from autologous blood, it is rich in sources, easy to get, simple to make, safe, and effective. According to the Chinese pain expert consensus (2022 edition) on the technical specifications for the preparation of autologous platelet-rich plasma, it can produce a large number of growth factors, which play an important role in accelerating wound healing, promoting tissue regeneration and repair, and relieving pain. Absolutely, blood is a valuable resource, and blood transfusion is a vital medical procedure, and cardiac surgery is a very risky type of surgery. Surgical procedures involving the cardiac aorta are potentially dangerous, often necessitating extracorporeal circulation (cardiopulmonary bypass, CPB) or even deep hypothermia, and frequently involving a high level of intraoperative outflow [3, 4]. Blood protection and restoration of clotting function are critical steps in aortic surgery [5], and the use of homologous blood and blood products is common in patients undergoing cardiac aortic surgery. Although autologous blood recovery machines are often used for extracorporeal circulation assistance during surgery, this process washes the blood to leave concentrated red blood cells, while the platelets and plasma are wasted by washing. Although CPB preserves the platelets and plasma, the destruction and activation of red blood cells, platelet function, and coagulation factors caused by heparinization and activation of pipeline materials, mechanical rolling, and other factors can inhibit postoperative renal function and coagulation, leading to high drainage volumes and even the need for secondary open-heart hemostasis [6]. Transfusion of allogeneic platelets and plasma is beneficial in the treatment of postoperative hemorrhage. The use of platelet-rich autologous plasma in patients undergoing aortic coarctation surgery is related with a decrease in intraoperative and postoperative blood transfusions in cardiac surgery [7]. PRP usage in aortic arch replacement surgery minimizes cryopresorptive transfer, raises postoperative serum albumin and total protein levels, and lowers the frequency of pleural effusion. PRP injection had no effect on other postoperative blood parameters or CTA readings [8]. PRP is used in many aspects of blood product use in cardiothoracic surgery [9]. However, the collection and storage of these components are difficult and expensive, with numerous potential complications.

ANH is a common clinical practice for blood conservation during autologous blood transfusion and has been used in a variety of procedures. ANH has been shown to reduce the use of postoperative blood products, drainage, and the rate of secondary open-heart hemostasis in patients undergoing cardiac surgery [10]. Blood separation has been shown to have a similar effect [11]. However, there is currently a lack of randomized controlled trials, and it has been suggested that its use should be limited to aortic surgery, with further information needed regarding its use during cardiac surgery.

Although some studies have confirmed the hemoprotective effects of ANH and blood separation in aortic surgery, no randomized controlled trials have compared these two methods. We designed a study to test the hypothesis that blood separation techniques may be more effective for restoring coagulation and reducing the need for allogeneic blood products.

## Methods

### Study design {8}

This is a prospective, single-center, double-blind controlled clinical trial comparing the use of autologous platelet-rich plasma (aPRP, experimental group) and autologous whole blood (ANH, control group) in patients undergoing aortic surgery. The main study objectives include the volumes of allogeneic blood and blood products needed. We also aim to compare the durations to aortic block, extracorporeal circulation, deep hypothermic arrest of circulation, and tracheal extubation, length of hospital stay, and the incidence and mortality of secondary surgical hemostasis or application of intra-aortic balloon pump (IABP) and extracorporeal membrane oxygenation (ECMO) in both groups. Heart rate, systolic blood pressure, diastolic blood pressure, central venous pressure, and thromboelastography (TEG) were also compared before blood reservation (T1), after blood reservation (T2), before blood reserving (T3), and after (T4) blood reserving.

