**Methods and analysis:**

This is a prospective, single-center, double-blind controlled clinical trial including 160 patients randomized 1:1 to receive aPRP (test group) or autologous whole blood (ANH, control group). The primary objective is to compare the drainage volumes in the two groups at 24, 48, and 72 h postoperatively. Secondary outcomes include input of allogeneic blood and blood products and durations of aortic block, extracorporeal circulation, deep hypothermic arrest of circulation, tracheal extubation, hospital stay, requirement for secondary surgical hemostasis, and application of intra-aortic balloon pump or extracorporeal membrane oxygenation in the two groups. In addition, heart rate, systolic blood pressure, diastolic blood pressure, central venous pressure, and thromboelastography recorded before blood reservation (T1), after blood reservation (T2), before blood transfusion (T3), and after the blood is returned (T4) to the transfusion will be compared between the two groups of patients.

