#### Inclusion and exclusion criteria

The inclusion criteria are patients undergoing aortic revascularization under deep hypothermic arrest circulation in an elective or emergency setting, and patients and families provided informed consent. The exclusion criteria are a history of previous cardiac surgery, preoperative hemoglobin < 90 gL, hematocrit < 30%, platelets < 100 × 10^9^L, and cardiac insufficiency, left ventricular ejection fraction < 50%, patients who died following surgery for a variety of reasons (hemorrhagic shock, heart failure, infection, etc.), or severe aortic stenosis. The discharge criteria are good recovery of cardiac function, hemodynamic stability maintained, and blood counts and other biochemical parameters are normalized.

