### Follow-up

Patients in this trial will be followed up by an investigator once a day on postoperative days 1–3 to record the drainage volume and the administration of IABP and ECMO.

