### Determination of sample size

We calculate the required sample size based on the drainage volume (mean ± standard deviation) at 24 h after the end of the manual procedure. Our preliminary study showed that the drainage volumes at 24 h postoperatively in the aPRP and control groups were 316 ± 102 and 378 ± 133 mL, respectively. Eighty patients per group were therefore needed to detect a difference with a power of 80% and a type I error rate of 5% using the PASS software.

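### Mortality is listed as an outcome in one sentence only; read literally it is mortality within a post-randomisation subset, and the exclusion criteria and follow-up section do not settle or support it

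*Protocol article*

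**What the plan says.** Four parts of the protocol article bear on mortality.

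- **Study design {8}** sets out the comparisons and includes "the incidence and mortality of secondary surgical hemostasis or application of intra-aortic balloon pump (IABP) and extracorporeal membrane oxygenation (ECMO) in both groups". No other sentence lists mortality as an outcome.
- **Abstract, Methods and analysis** has a list that opens "Secondary outcomes include input of allogeneic blood and blood products and durations of aortic block, extracorporeal circulation, deep hypothermic arrest of circulation" and closes with "requirement for secondary surgical hemostasis, and application of intra-aortic balloon pump or extracorporeal membrane oxygenation in the two groups". These are the same re-exploration and device items, without mortality.
- **Inclusion and exclusion criteria** names, among the exclusions, "patients who died following surgery for a variety of reasons (hemorrhagic shock, heart failure, infection, etc".
- **Follow-up** has an investigator see patients "once a day on postoperative days 1–3 to record the drainage volume and the administration of IABP and ECMO". Death is not among the items named.

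The horizon also varies. The retention section {18b} describes monitoring until the patient leaves the PACU, the Follow-up section covers three postoperative days, and the section on blinding and allocation concealment mentions follow-up in connection with discharge.

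**The concern.** In the Study design sentence, incidence and mortality share one object: re-exploration, IABP or ECMO. On that grammar the denominator for mortality is the patients who had one of those events.

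These events happen after randomisation, and re-exploration for bleeding is something the test treatment might reduce. If it prevents the milder re-explorations, the patients left in that subset are sicker on average, and mortality among them rises in the arm that did better. If it prevents the severe ones, the distortion runs the other way. Deaths outside the subset are not counted at all, and the article itself gives infection as a cause of death that need not involve re-exploration or a device.

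What is at stake is whether a difference in drainage can be read next to an interpretable survival comparison in high-risk surgery. While the denominator is open, it could also be chosen after the data have been seen.

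**Working it through.** The article states no mortality rate, mortality hypothesis or power for mortality, so there is no planned figure to reproduce. The check is a comparison of the text, followed by an illustration with assumed counts.

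**Step 1. The sections side by side.**

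| Section | Mortality an outcome? | What it implies for the denominator |
|---|---|---|
| Study design {8} | Yes | Literal reading: patients with re-exploration, IABP or ECMO. Looser reading: each randomised group |
| Abstract | Not listed | None |
| Exclusion criteria | No | Patients who died after surgery are taken out |
| Follow-up | Death not named | None; days 1–3 only |

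Post-operative death cannot be known at enrolment, so as an exclusion it can only act after randomisation. If it is applied, the numerator for post-operative death is zero in both arms, whichever denominator is used. It therefore conflicts with the Study design sentence under both readings.

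**Step 2. What the literal reading can do.** The counts are assumed, with 80 patients per arm (160 randomised 1:1). In every row each arm has 2 deaths, so all-patient mortality is 2/80 = 2.5% in both arms. The control arm always has 8 re-explorations, with both deaths among them: 2/8 = 25%.

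| aPRP arm (assumed) | Subset mortality, control vs aPRP | All randomised |
|---|---|---|
| 4 re-explored, both deaths among them | 25% vs 2/4 = 50% | 2.5% vs 2.5% |
| 8 re-explored, both deaths among them | 25% vs 2/8 = 25% | 2.5% vs 2.5% |
| 4 re-explored, both deaths elsewhere (e.g. infection) | 25% vs 0/4 = 0% | 2.5% vs 2.5% |

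With identical mortality, the subset difference (aPRP minus control) runs from 50 − 25 = +25 percentage points to 0 − 25 = −25 points.

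**Step 3. Precision.** The exact (Clopper–Pearson) 95% interval for x deaths in n has as lower limit the 0.025 quantile of Beta(x, n − x + 1) and as upper limit the 0.975 quantile of Beta(x + 1, n − x).

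- 2/8: 3.2% to 65.1%
- 2/4: 6.8% to 93.2%
- 2/80: 0.3% to 8.7%

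**Step 4. What the all-randomised comparison can deliver.** For two proportions, two-sided 5%, n = 80 per arm and mean proportion p̄, power = Φ{[|p1 − p2| − 1.96 √(2p̄(1 − p̄)/n)] / √([p1(1 − p1) + p2(1 − p2)]/n)}. The mortality rates are assumed.

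- 10% vs 5%: (0.05 − 1.96 × 0.04165)/0.04146 = −0.76, power about 22%
- 15% vs 5%: (0.10 − 1.96 × 0.04743)/0.04677 = 0.15, power about 56%

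The correct denominator removes the bias but does not make the trial informative about modest survival differences.

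**The case against.** The strongest reply is that the subset denominator is inferred. The sentence sits in a list of by-group comparisons, ends by referring to both groups, and can be read as the incidence of these events, plus mortality, per randomised arm. That stands. A reader might infer that deaths will certainly be compared on a subset or not at all; the article does not say so, and the all-patient reading remains open.

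A reader might also take the abstract as a second definition that drops mortality. The article does not support that either: an abstract is condensed, and its list is introduced with a verb of inclusion, so its silence is not a rule. The abstract simply does not help to choose between the readings.

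It can be added that a journal article may leave denominators to a full protocol or analysis plan. That would answer a complaint about missing detail. It does not answer a sentence whose literal sense gives a poor comparison, or an exclusion criterion that contradicts it.

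Finally, the counts in the illustration are chosen. They show that the distortion is possible and can run in either direction; they do not show that this trial will incur it. The imprecision of the all-patient comparison is also conceded, and it limits what the fix gains.

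**Conclusion.** The point holds as one of ambiguity and internal conflict. Mortality is listed as an outcome once. The literal wording there gives a non-randomised comparison, a by-group reading is possible, and no other section decides between them. The exclusion of patients who died after surgery, if applied as written, empties the comparison under both readings, so rewording the outcome sentence alone would not be enough.

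No size can be derived from the article. Under the assumed counts, equal mortality of 2.5% per arm can appear as a subset difference anywhere from −25 to +25 percentage points. The conclusion about bias rests only on re-exploration and device use being post-randomisation events that treatment can affect. The primary outcome, drainage, does not depend on how mortality is defined, but the exclusion of deaths touches it too, because hemorrhagic shock is one of the named causes.

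**What to change.** Reconcile the abstract, Study design {8}, Inclusion and exclusion criteria and Follow-up so that they say one thing:

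1. Re-exploration for bleeding, IABP use and ECMO use, each as a proportion of all randomised patients in the arm.
2. All-cause in-hospital mortality as a separate secondary safety outcome, with all randomised patients in the arm as denominator.
3. Post-operative death no longer a ground for removal from the analysis set.
4. Deaths among patients with re-exploration or device support listed descriptively, with no between-arm test in that subset.
5. Death up to hospital discharge added to the recorded items.

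The cost is small. Length of hospital stay is already an outcome, so each patient's course to discharge has to be known, and no visit, procedure or patient is added. Keeping the deaths means stating how drainage at 24, 48 and 72 h is handled for a patient who dies before 72 h. With 80 per arm the mortality comparison will be imprecise; it should be given as counts and proportions with exact intervals, as descriptive safety information.

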### Study site and patient selection

#### Patients

A total of 160 patients undergoing aortic surgery at the Department of Cardiac Surgery, First Affiliated Hospital of China Medical University, Shenyang, Liaoning Province, China, from July 1, 2019, will be recruited. All patients were randomly divided into two groups in a 1:1 ratio. The purpose and potential risks and benefits of this study will be fully explained to the patients and their families and informed consent will be obtained prior to the procedure.

#### Enrolling{16c}

The computer is responsible for assigning sequences, randomly assigning patients to groups A and B. After seeing the patient, the anesthesiologist is in charge of recruiting participants.

#### Who will take informed consent? {26a}

Informed consent is obtained from the anesthetist during the pre-operative visit or from the blinded members of the study team on the day of surgery. Written informed consent is also required from the patient’s legal representative and the investigator before any study-related procedures are started.

#### Additional consent provisions for collection and use of participant data and biological specimens {26b}

Not applicable. Collection of biological samples is not required.

#### Inclusion and exclusion criteria

The inclusion criteria are patients undergoing aortic revascularization under deep hypothermic arrest circulation in an elective or emergency setting, and patients and families provided informed consent. The exclusion criteria are a history of previous cardiac surgery, preoperative hemoglobin < 90 gL, hematocrit < 30%, platelets < 100 × 10^9^L, and cardiac insufficiency, left ventricular ejection fraction < 50%, patients who died following surgery for a variety of reasons (hemorrhagic shock, heart failure, infection, etc.), or severe aortic stenosis. The discharge criteria are good recovery of cardiac function, hemodynamic stability maintained, and blood counts and other biochemical parameters are normalized.

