#### Double-blind randomization and allocation concealment

Enrolled patients undergoing aortic surgery will be divided randomly into a control group (ANH) and an aPRP group using a computer-generated sequence. Groups will be chosen before patient admission, and all patients and staff will be oblivious to their group assignment. The anesthesiologist will not be informed of the patient assignments, which are recorded and sealed in sequentially numbered opaque envelopes. Nurse anesthetists can give sealed envelopes and tell to prepare the items for the experiment based on group allocations; there are no differences in the look of the two sets of envelopes. The group assignment will be withheld from all patients and anesthesiologists. Following anesthesia induction, the anesthesiologist may perform the various surgeries in accordance with the coded number. Another anesthesiologist will document intraoperative data and followed up on the patient’s discharge. Finally, the data will be analyzed by a professional statistician.

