### The treatment of non-adherence and missing data{20c}

If there is a clear violation of the protocol, the trial should be stopped, and the subject’s data should be blinded and not included in the final statistical results; if it can be adjusted in time and does not make a significant difference, the data set can be retained. If there are missing data cases, replacement of the data can be tried if necessary, based on the dataset’s characteristics and qualities.

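### Death after surgery, including from hemorrhagic shock, is listed as an exclusion criterion, so randomised and treated patients are removed on a consequence of the bleeding outcome

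*Protocol article*

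**What the plan says.** In the protocol article, the section on inclusion and exclusion criteria mixes baseline conditions (previous cardiac surgery, low hemoglobin, hematocrit or platelets, poor ejection fraction, severe aortic stenosis) with one event that is not a baseline condition: "patients who died following surgery for a variety of reasons (hemorrhagic shock, heart failure, infection, etc".

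The section on double-blind randomization and allocation concealment sets the order of events. "Groups will be chosen before patient admission", and the allocated procedure comes later: "Following anesthesia induction, the anesthesiologist may perform the various surgeries in accordance with the coded number".

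The outcome is given in the abstract: "The primary objective is to compare the drainage volumes in the two groups at 24, 48, and 72 h postoperatively". The conclusion sought is "if the use of aPRP could reduce the risk of bleeding after aortic surgery compared with ANH". Study design {8} adds to the comparisons "the incidence and mortality of secondary surgical hemostasis or application of intra-aortic balloon pump (IABP") and ECMO.

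No section defines an all-randomised analysis set or limits the exclusion of patients who died. Two other places also remove patients after randomisation. Under General anesthesia, a case is dropped if the collected blood is needed for extracorporeal circulation. The section on non-adherence and missing data says that data from clear protocol violators are "not included in the final statistical results".

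**The concern.** Eligibility criteria should be decidable before allocation. This one depends on what happens after treatment. Hemorrhagic shock, the first cause of death named, is the extreme form of what the primary outcome measures. Deaths from heart failure or infection may also depend on treatment.

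If these patients leave the data set, the groups compared are no longer the randomised groups. Should one technique cause or prevent fatal bleeding, the drainage comparison is distorted. So are the comparisons of transfusion, re-exploration, IABP or ECMO use, extubation and hospital stay. An arm with more fatal bleeding could look equal to the other arm, or better. The rule also removes the patients on whom any mortality comparison depends.

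**Working it through.** **1. When can the rule act?** Allocation comes before admission, the allocated procedure follows induction, surgery comes next, and death after surgery comes last. The criterion therefore always applies after randomisation and treatment. Reading it as a withdrawal rule changes nothing, because the patient still leaves the comparison.

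**2. Planning figures** (Determination of sample size): 24 h drainage 316 (SD 102) mL with aPRP and 378 (SD 133) mL with ANH, 80 per arm, 80% power, 5% type I error (two-sided assumed).

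- Difference = 378 − 316 = 62 mL.
- Pooled SD = √((102² + 133²)/2) = 118.5 mL.
- These inputs need 58 per arm (normal approximation) or 59 (t test), not 80. With 80 per arm, power is about 91%. That mismatch is a separate matter, and the 91% serves here only as the reference.

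**3. Illustration.** The documents give no death rate. The rates below, and the assumption that deaths are exactly the highest drainage values in a normal distribution, are mine. The assumption is extreme.

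Removing the top fraction q lowers the mean by SD × h, with h = φ(z)/(1 − q), where z is the upper-q normal quantile. The SD becomes SD × √(1 − z·h − h²).

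- q = 5%: z = 1.645, h = 0.109. The mean falls by 14.4 mL in ANH or 11.1 mL in aPRP.
- q = 10%: z = 1.282, h = 0.195. The mean falls by 25.9 mL in ANH or 19.9 mL in aPRP.

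| Removed (ANH / aPRP) | Observed difference |
|---|---|
| none | 62 mL |
| 10% / 5% | 62 − 25.9 + 11.1 ≈ 47 mL |
| 5% / 10% | 62 − 14.4 + 19.9 ≈ 67 mL (67.5 mL) |
| 10% / 10% | 62 − 25.9 + 19.9 = 56 mL |

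The last row shows that equal removal is not neutral when the two SDs differ.

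**4. Power in the 10% / 5% case.** Truncation also shrinks the SDs: ANH 133 × √(1 − 1.282 × 0.195 − 0.195²) ≈ 112 mL, and aPRP 102 × √(1 − 1.645 × 0.109 − 0.109²) ≈ 92 mL. With 72 ANH patients, 76 aPRP patients and a 47 mL difference, the noncentral t gives about 80% power.

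**5. Milder version.** A simulation with the planning means and SDs dropped half of the patients above 600 mL (0.1% of aPRP and 2.4% of ANH). The difference fell from 62 to about 56 mL.

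**6. Deaths unrelated to drainage.** Excluding 5% to 25% at random leaves 89% to 81% power and does not bias mean drainage.

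**The case against.** The numbers describe an extreme case. The criterion names heart failure, infection and other causes as well as hemorrhagic shock, and no death rate is given. Deaths unrelated to drainage would not bias the drainage means. The reversed-rate case moves the estimate by only about 5.5 mL, and the mild simulation by about 6 mL. All of this stands, and it limits what can be said about size.

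Three stronger readings are tempting, and the documents do not support them.

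- *The trial loses much of its power.* A reader who lowers the means but keeps the planning SDs would get about 67% in the 10% / 5% case. That combines truncated means with untruncated SDs. Done consistently, power is about 80%, which is the protocol's own target.
- *Mortality becomes zero versus zero.* The phrase "the incidence and mortality of secondary surgical hemostasis" and the words after it may tie mortality to re-exploration, IABP and ECMO rather than mean all-cause death by arm. The abstract's secondary outcomes do not list mortality. Nor does the article say that excluded deaths will never be tabulated. What stands is that the two sections conflict and must be reconciled.
- *The bias favours a known arm.* The documents do not fix its direction.

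None of this rescues the rule. No section limits it, and a criterion written into the article is not a detail left to a fuller document.

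**Conclusion.** The criterion is wrong as written and should be corrected before analysis. That conclusion rests on the order of events in the protocol, not on any assumed death rate: the rule removes randomised, treated patients on a consequence of the primary outcome, so the comparison is conditioned on survival.

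The size and direction of the resulting bias cannot be determined from the documents. Under the extreme assumption, the 62 mL planned difference could be observed as anything from about 47 to about 67 mL at death rates of 5% to 10%. The main harm is bias. The fall in power from about 91% to about 80% in the less favourable case is secondary.

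**What to change.** 1. Delete death after surgery from the exclusion criteria.
2. Analyse all randomised patients in their assigned group.
3. Prespecify the handling of death separately for 24, 48 and 72 h. A patient who dies before a given time takes the worst rank at that time in a rank-based comparison. A patient who dies later contributes the drainage observed. Do not use the volume collected up to death as the value, because a patient who dies early of hemorrhage could then count as a low bleeder.
4. Report deaths by arm, and reword Study design {8} so that it is clear which mortality is compared.
5. For extubation time and hospital stay, count death as a failure, not as an exclusion.

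The cost is an amendment and some analysis text. A rank-based result is harder to read in mL, and variance may be slightly larger. Recruitment started on July 1, 2019, so data on any patients already excluded for death must be recovered where they exist. The article does not say whether such data were kept.
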